#### 3.5 Dose Rationale / Medical Device: Rationale for the intended purpose in the study (pre-market MD)

The main aim of this study is to focus on the safety and feasibility of US-G VPS placement, with a special interest lying on the surgical intervention time (primary outcome). No preplanning, head fixation, or preoperative registration is needed. It is a real-time navigation method with direct visualization of the correct catheter placement.

US itself is not known to have any harmful side effects and does not contain harmful radiation, therefore it would be an optimal solution in the daily practice for routine use in all patients, especially in children and pregnant women.

### 3.6 Explanation for the choice of the comparator (or placebo)

Stereotactic navigated VPS placement is in use for many years. It has great accuracy even with slit ventricles. During navigation, pre-planned images can be seen without real-time correction, as opposed to US guidance. Preplanning, head fixation, and preoperative registration are mandatory, possibly prolonging surgical intervention time and therefore leading to higher operating costs and longer duration of anesthesia.

No prospective data is available for comparison of US-G and stereotactic navigated VPS placement.

### 3.7 Benefits / Risks

US navigation: Compared to stereotactic navigation its use is fast with almost no extra time and extra cost, it does not need head fixation, preoperative planning nor referencing, thus shortening surgical intervention time. With real-time guidance, there is a correction for brain shift and new space-occupying lesions distorting the ventricular anatomy.

One of the main limitations of US is that a learning curve exists at first and that quality and understanding of US images can be limited, leading, at first, to longer surgical times. For placement of the burr hole probe on the cortex and insertion of the catheter with US guidance, the burr hole needs slight enlargement. This is a technical matter easily solved by a Kerrison punch, or by the placement of two overlapping burr holes resulting in a lying eight.

Stereotactic navigation: The method has great accuracy even in pediatric patients and patients with slit ventricles. The patient's head needs to be fixed in a head clamp and the exact location of the entry point, the trajectory and the length of the catheter are pre-planned on the preoperative CT imaging. Fixation of the head with a head clamp holds risks for complications such as bleeding or infection. Planning and referencing of the navigation is time-consuming and prolongs the anesthesia time. The time factor is also a problem in an emergency operation. Since this is not a real-time navigation method, there is no correction for brain shift e.g. after placement of the burr hole (when air is entering the skull) or for new space-occupying lesions occurring in the time between the CT scan, and the operation.

### 3.8 Justification of choice of the study population

The study population will consist of patients above the age of 18 years receiving a VPS due to any reason. The study population includes vulnerable participants. In patients not capable of judgment (e.g. dementia/ neurologic state) informed consent of the next of kin will be obtained. Signs and symptoms showing that the participant is unwilling to participate in the study will result in the participant being excluded from participating.

## **4. STUDY OBJECTIVES**

### **4.1 Overall Objective**

- The main purpose of this study is to prospectively evaluate the feasibility of US navigation compared to stereotactic navigated VPS placement.

### **4.2 Primary Objective**

To assess for the feasibility of the US navigation method we chose the surgical intervention time for comparison between the two navigation methods, which is a very well standardized time in minutes and is recorded for every operation. Any navigation method will probably prolong the time spent in the OR, but the time spent for US navigation will eventually be shorter than the time spent for stereotactic navigation, what would be very interesting in terms of cost efficiency, and burden for the patients (since additional anaesthesia time might be harmful).

### **4.3 Secondary Objectives**

Further we are interested in special aspects of safety and feasibility of the navigation methods in direct comparison to each other, such as positioning of the catheter (optimal/not optimal, grade I to IV, safety), rate of VPS dysfunction and revision surgery (safety), number of ventricular puncture attempts that have been made (safety and feasibility), operation and anaesthesia times (feasibility), and any complications and morbidity (safety), as well as death (safety).

### **4.4 Safety Objectives**

- Perioperative complications and mortality will be assessed for (see 4.3).

## 5. STUDY OUTCOMES

### 5.1 Primary Outcome

The primary outcome is the surgical intervention time. This is the time spent in the OR by the surgeon and includes the preparation time together (patient positioning, head clamping in the stereotactic navigation group) with the operation time of the neurosurgical part. Beginning (“Lagerung”) and ending (“Naht neurosurgical part”) of this time interval is clearly defined and will be in a standardized manner recorded by blinded anaesthesiologists. In the stereotactic navigation group, an additional 5 minutes will be added to the surgical intervention time for the preplanning of the navigation the day before the operation on the Brainlab workstation.

[figure not shown]

Figure 1: Composition of the surgical intervention time (preparation time plus operation time neurosurgical part), plus additional five minutes in the stereotactic navigation group.

### 5.2 Secondary Outcomes

- Secondary outcomes are:
  - Operation time in minutes (time in minutes from “Schnitt” to “Naht”)
  - Anaesthesia time in minutes (time in minutes from “Beginn Anästhesie” to “Ende Anästhesie”)
  - Number of puncture attempts
  - Catheter placement (optimal vs. not optimal): Optimal catheter placement has been defined as free-floating within the CSF without touching the ventricle wall or septum pellucidum, and the tip of the catheter located at the foramen of Monro showing an optimal length of the catheter. Catheters that did not fulfill all criteria have been defined as not optimal placed. Positioning of catheters will be further graded according to Yim et al. into grades I to IV (grade I: catheter terminates in the ipsilateral frontal horn, grade II: catheter terminates in contralateral frontal horn, grade III: catheter terminates in non-targeted CSF spaces, grade IV: catheter terminates intraparenchymally).
  - Volumetry of side ventricles pre- and postoperatively in cm^3 (number and relative change)
  - Evan’s Index pre- and postoperatively (number and relative change)
  - Complications (infection, bleeding, complications ass. with navigation method), mortality
  - Revision surgery (yes/no) and reason for revision

### 5.3 Other Outcomes of Interest

N/A

### 5.4 Safety Outcomes

- The positioning of the catheter
- Number of ventricle puncture attempts
- VPS dysfunction, the revision rate
- perioperative complications (bleeding, infection), complications due to head clamp
- death, coma (<1% expected)

## 6. STUDY DESIGN

### 6.1 General study design and justification of design

- This is a prospective, randomized controlled study in a superiority fashion. The primary outcome (surgical intervention time) is well standardized and recorded by anaesthesiology for every operation. Some of the secondary outcomes are measured by a blinded neuroradiologist. The method of randomisation is 1:1. We chose this study design, in order to achieve evidence of the best quality while minimizing possible bias.

Patients will be randomized in two groups at admission in a 1:1 rate: US or stereotactic navigation group. Randomisation will be stratified for age (under 40 years vs. over 40 years). On the day of the elective operation, the VPS will be placed with the randomized navigation method. The patient is blinded for the navigation method, but there is no possibility to perform this study in a double-blinded fashion since the surgeon cannot be masked to the method. All patients in the stereotactic navigation group need to have a CT scan that is not older than 5 days counted backwards from the operation day. In the US navigation group there will be performed a new CT at admission if the old scan (CT or MRI) is older than 90 days. In patients allocated to stereotactic navigation the entry point, trajectory, and length of the catheter will be pre-planned the day before the operation on the 1 to 5 days old CT scan. The patients allocated to US navigation will not receive any pre-planning.

All adult (> 18 years) patients receiving a VPS in an elective, semi-elective, or urgent manner will be included in the study. These patients suffer from different forms of hydrocephalus (e.g. hydrocephalus internus (malresorptivus, occlusivus), hydrocephalus externus, hydrocephalus communicans, normal pressure hydrocephalus) due to different diseases, thus creating a heterogeneous population. For each group we plan to include 65 patients, giving a total of  $130 + 6 = 136$  patients and hence a study duration of 4 years.

The primary outcome (surgical intervention time) is recorded in a standardized manner by anaesthesiology for every operation in our department. In the stereotactic navigation group, 5 minutes will be added to the surgical intervention time accounting for navigation preplanning. Some of the secondary outcomes (catheter placement (optimal vs. not optimal, grade I to IV), volumetry of side ventricles, Evans' Index) will be analysed by a blinded neuroradiologist.

At admission, demographic and medical history will be obtained from the patients. Neurologic examination with analysis of GCS, modified Rankin Scale (mRS), Glasgow Outcome Scale (GOS) will be performed, and neurological symptoms (headaches, vomitus, gait disturbances, urinary incontinence, dementia, coma, delir) will be recorded. Patients in the US group need to have a CT scan that is not older than 90 days (old CT scans can be used if not older than 90 days, otherwise a new CT scan will be performed at admission), and patients in the stereotactic navigation group will receive a CT scan on the day of admission. From this CT scan, the Evans' index will be measured and volumetry of the side ventricles will be done. In the stereotactic navigation group, the CT scan is used for pre-planning and referencing of the stereotactic navigation.

At day 0 (operation day) surgical intervention time, operation time and anaesthesia time, the number of puncture attempts, and peri-, as well as postoperative, complications will be assessed.

Postoperative during the hospital stay a CT scan will be performed (between 2nd and 5th day) for analysis of catheter positioning (optimal vs. not optimal, grade I to IV), volumetry of the side ventricles, and Evans' index. Neurologic examination with analysis of GCS, modified Rankin Scale (mRS), Glasgow Outcome Scale (GOS) will be performed, and neurological symptoms (headaches, vomitus, gait disturbances, urinary incontinence, dementia, coma, delir) will be recorded. Postoperative complications such as bleeding, rate of revision surgery and reason for revision, duration of hospital stay in days, duration of ICU stay in days, and peri-/postoperative complications will be assessed.

The first follow-up will take place 6-8 weeks postoperatively. Neurologic examination with analysis of GCS, modified Rankin Scale (mRS), Glasgow Outcome Scale (GOS) will be performed, and neurological symptoms (headaches, vomitus, gait disturbances, urinary incontinence, dementia, coma, delir) will be recorded. Assessment of postoperative complications (bleeding, complications due to head clamp, VPS infections, death), as well as type and reason for revision surgery, will be made.

The second follow-up will be performed 6 months postoperatively and includes a cCT scan (catheter position (optimal vs. not optimal, grade I to IV), calculation of Evans' index, volumetry of side ventricles), neurologic examination (analysis of GCS, modified Rankin Scale (mRS), Glasgow Outcome Scale (GOS), and neurological symptoms (headaches, vomitus, gait disturbances, urinary incontinence, dementia, coma, delir)), analysis of postoperative complications (bleeding, complications due to head clamp, VPS infections, death), and type and reason for revision surgery.

## **6.2 Methods of minimising bias**

### **6.2.1 Randomisation**

Randomisation will be performed by an independent individual using a stratified simple randomisation procedure as implemented in the electronic data capture software REDCap. An allocation ratio of 1:1 ensure a balance in sample size across both groups over time. The randomisation has been stratified according to age of the patients (under 40 years/over 40 years).

### **6.2.2 Blinding procedures**

- Participants will be blinded for the navigation method they are randomized to. There is no possibility to blind the treating physician since he has to place the VPS with the selected navigation method and stereotactic navigation needs a pre-planning the day before the operation. The primary outcome is recorded by the anaesthesiology (not involved doctor), and some of the secondary outcomes will be measured by a blinded neuroradiologist who does not know the selected navigation method.

### **6.2.3 Other methods of minimising bias**

- Prospective acquisition of data through CRF forms through an electronic software (REDCap).

## **6.3 Unblinding Procedures (Code break)**

- Since the treating physicians are not blinded for the allocated intervention, there is no need for specific unblinding procedures.

## 7 STUDY POPULATION

### 7.1 Eligibility criteria

Participants fulfilling all of the following inclusion criteria are eligible for the study:

- Informed Consent as documented by signature (Appendix Informed Consent Form)
- Patients undergoing elective or emergent VPS placement
- frontal or occipital shunt placement
- Patients older than 18 years

The presence of any of the following exclusion criteria will lead to exclusion of the participant:

- Patients under the age of 18 years
- No informed consent.
- Emergency surgery if there is no time for installation of any navigation system
- Revision surgery using the same side and location, or revision surgery where no completely new shunt will be placed
- Ventriculoatrial and ventriculopleural placement
- Women who are pregnant or breast feeding
- Intention to become pregnant during the course of the study
- Enrolment of the investigator, his/her family members, employees, and other dependent persons

### 7.2 Recruitment and screening

Recruitment will take place either in the neurosurgical outpatient clinic or in the ER-Department of the University Hospital of Basel. The recruitment will be done by one of the clinics physicians who will be trained for this particular study. There will be no payment or compensation given to the participants.

### 7.3 Assignment to study groups

All patients entering the hospital for elective or emergent VPS surgery will be randomized in 1:1 fashion to one of the study groups at admission or the day before the operation. The randomisation process is further described in chapter 6.2.1. and will be performed by one of the trained physicians using the REDCap software.

### 7.4 Criteria for withdrawal/discontinuation of participants

Patients will be withdrawn from the study in case of withdrawal of informed consent or non-compliance, as well as patients with VPS dysfunction receiving revision surgery on the same side and location. If the surgeon shows non-adherence to the allocated navigation method (estimated in 1% of all cases), the patient will also be included, but will be included in the as treated analysis. Patients will not be replaced.

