### 8.4 Compliance with study intervention

During the perioperative period, compliance to the randomized navigation method will be monitored by study nurses. In cases of switched navigation method pre- or intraoperatively (see 8.3.) the reasons will be recorded and there will be an intention-to-treat analysis.

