### 9.2.5 Assessments in participants who prematurely stop the study

No further assessments will be performed for such patients.

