### 11.2 Determination of Sample Size

The sample size was estimated with the aim of showing a surgical intervention time reduction of 15 minutes (min) in the intervention arm compared to the control arm. The significance level was chosen to be 5%, while the power was chosen to be  $(1-\beta) = 80\%$ .

Based on unpublished data from a pilot study assessing the surgical intervention time in patients undergoing VPS placement using US navigation, we calculated a mean surgical intervention time of 63 min with a standard deviation (SD) of 28.65 min. Because of the additional steps involved using stereotactic navigated surgery we assume an increased surgical intervention time in those patients. Based on these assumptions we calculated various scenarios presuming different differences in surgical intervention time between the two arms (see Figure 9).

For our hypothesis for the sample size calculation, we then conservatively selected a scenario with a relatively modest difference between groups. This resulted in 58 patients with VPS placement surgery per group. Anticipating a 1% drop-out by deaths and a surgeons' non-adherence rate (change from control to treatment arm) of 5%, a total sample size of  $130 + 6 = 136$  patients (68 per group) is required (see Figure 9).

[figure not shown]

Figure 9: Sample size for different scenarios with 80% power and  $\alpha = 0.05$ . The calculation is based on a standard deviation in surgical intervention time of 28.65 min with an anticipated drop-out rate of 1% and a non-compliance rate (change of treatment arm) of 5%.

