#### **11.4.1 Datasets to be analysed, analysis populations**

The full analysis set (FAS) will include all patients that were randomized. All statistical analyses will be performed on the FAS according to the intention-to-treat principle (i.e. all participants will be analysed on the basis of the intervention to which they were randomly allocated).

The per-protocol (PP) set will include all participants in the FAS who fulfilled the eligibility criteria, for whom the surgery was completed as planned in the study protocol, and for whom the measurement of the primary outcome is available.

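### Protocol 7.4 makes undefined non-compliance a ground for withdrawal after randomisation, so outcomes can be lost in a way related to patients' health

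*Combined protocol and SAP*

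**What the plan says.** Protocol 7.4 opens: "Patients will be withdrawn from the study in case of withdrawal of informed consent or non-compliance". It adds a third ground, revision surgery at the same site, which is a separate matter. It also says that patients are not replaced.

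The next sentence of 7.4 deals with switched methods: "If the surgeon shows non-adherence to the allocated navigation method (estimated in 1% of all cases), the patient will also be included", and continues "but will be included in the as treated analysis".

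The protocol uses the idea of compliance in two other places:

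- Section 8.4: "compliance to the randomized navigation method will be monitored by study nurses". For switched patients it adds that "the reasons will be recorded and there will be an intention-to-treat analysis".
- The Figure 9 caption in 11.2 gives a non-compliance rate of 5% and explains it in brackets as a change of arm.

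Two sections cover what happens after a patient leaves. Section 9.2.5, on premature stopping, says "No further assessments will be performed for such patients". Section 8.5 has withdrawn patients seen at 6-8 weeks and again at 6 months with a CT, but as non-participants.

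The analysis sets differ. Protocol 11.4.1 says "The full analysis set (FAS) will include all patients that were randomized". SAP 4.4 restricts the same set to randomised patients who completed follow-up, without drop-outs, although SAP section 7 reports no changes from the protocol. SAP 6.3.1 analyses by allocation whatever treatment was received.

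The sample size in 11.2 allows for loss as follows: "Anticipating a 1% drop-out by deaths", plus 5% for surgeons' non-adherence.

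**The concern.** The intervention is one operation, and the primary outcome is complete that day. What a patient can still fail to do afterwards is mostly to attend visits and scans. A rule that withdraws patients for this can turn one missed visit into the end of data collection for dysfunction, revision, complications and death, all of which are collected to 6 months.

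Such losses are unlikely to be random. Section 2.6 expects at least half of the patients to belong to a vulnerable group, for example because of dementia or impaired consciousness. Patients too unwell to attend may also be those more likely to have had an event.

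The SAP adds a consequence for the primary endpoint. If a withdrawn patient has not completed follow-up, SAP 4.4 read literally removes that patient from the full analysis set, together with a surgical intervention time that was already measured.

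**Working it through.** **Two readings of the term**

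| Reading | Where 7.4 leads | Text that conflicts |
|---|---|---|
| Missed visit or CT | Withdrawn; assessment ends (9.2.5); out of the SAP 4.4 set | 8.5 continues visits, as a non-participant; 11.4.1 keeps all randomised |
| Switched method (Figure 9 caption; sense of 8.4) | Withdrawn | Next sentence of 7.4; 8.4; 11.4.1; SAP 6.3.1 |

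The second reading has its own size. Section 11.2 describes the 5% as a change from control to treatment, which is 0.05 × 68 = 3.4 patients. Applied to both arms it is 0.05 × 136 = 6.8. At the 1% given in 7.4 it is 0.01 × 136 = 1.4.

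**Patients and events affected under the first reading**

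The withdrawal rate w is not in the documents, so I assume 5-10%. The revision rate is also assumed, at 15%.

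- Patients: 0.05 × 136 = 6.8 and 0.10 × 136 = 13.6, so about 7-14.
- Revision events among them: 6.8 × 0.15 = 1.0 and 13.6 × 0.15 = 2.0.
- Expected in the whole trial: 136 × 0.15 = 20.4.

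This applies the average rate to the withdrawn patients. If loss is related to health, their rate would be higher, by an amount the documents cannot supply.

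**The plan's sample size**

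Inputs from 11.2 and SAP 4.2: difference 15 min, SD 28.65 min, two-sided 5%, power 80%.

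n = 2 × (1.96 + 0.8416)² × 28.65² / 15² = 57.3, so 58 per group, as stated.

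Inflation: 58 / 0.95² / 0.99 = 64.9, so 65 per group and 130 in total, as stated. The text does not derive the further 6 patients that give 136. The allowance covers deaths and method switches only.

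**Power if withdrawn patients leave the analysis set**

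Power = Φ(δ / (28.65 × √(2/m)) − 1.96), with m = N(1 − w) per arm. δ is 15 min, or 15 × 0.95 = 14.25 min when diluted by 5% crossover. Example: N = 65, w = 5%, δ = 14.25 gives m = 61.75, a standard error of 5.16, and Φ(2.76 − 1.96) = 78.9%.

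| w | 65 per arm, 15 min | 65 per arm, 14.25 min | 68 per arm, 15 min | 68 per arm, 14.25 min |
|---|---|---|---|---|
| 0% | 84.7% | 80.9% | 86.3% | 82.6% |
| 5% | 82.9% | 78.9% | 84.5% | 80.7% |
| 10% | 80.8% | 76.7% | 82.5% | 78.6% |

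A 10% loss costs about 4 percentage points.

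**Possible bias in the primary outcome**

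If a share w of one arm is excluded and its mean time differs from the retained patients' mean by D, that arm's mean moves by w × D. With w = 5% and D = 10 min this is 0.5 min; with w = 10% and D = 30 min it is 3.0 min, against a target difference of 15 min. Equal exclusion of similar patients in both arms would largely cancel. Both w and D are assumptions.

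**The case against.** Several stronger conclusions are tempting, and the documents do not carry them.

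- **That the term can only mean a missed visit or a switch.** This is an inference. It could also mean refusing an examination or other study procedure without formally withdrawing consent. Sections 2.6 and 3.8 already exclude patients who show signs of unwillingness. No text says that a single missed visit triggers withdrawal, and SAP 5.4 lists withdrawals and losses to follow-up as different things.
- **That this word breaks intention-to-treat.** The next sentence of 7.4 keeps patients whose surgeon switched method, and 8.4 and SAP 6.3.1 do the same. The clearer intention-to-treat conflict in 7.4 is its as-treated wording, which would remain if only the non-compliance ground were removed.
- **That all later outcomes are discarded.** Section 8.5 provides visits to 6 months with CT. Its conflict with 9.2.5 is unresolved, and nothing says whether data from non-participants enter the analysis. Outcomes can be lost; it is not established that they are.
- **That several events would vanish from one arm.** At the assumed rates, 1-2 revision events are lost across both arms, and nothing in the plan shows a mechanism that differs between arms.
- **That the loss is a multiple of the 1% allowance.** That allowance was set for an outcome recorded on the operation day and was never meant for 6-month follow-up.

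It is also fair to say that protocol 11.4.1 keeps every randomised patient, and that SAP 6.3.1 and 6.4 speak of imputing missing primary outcomes, which sits badly with a completers-only set. So removal of the operation-day outcome is a literal consequence of SAP 4.4, not a certain one.

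What stands is an operative rule that withdraws randomised patients on an undefined ground, next to sections that disagree on what follows.

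**Conclusion.** The point holds as a defect in the withdrawal rule that should be amended. Under the missed-visit reading, safety outcomes to 6 months can be lost in a way related to health, and SAP 4.4 can take the primary outcome with them. Under the Figure 9 reading, 7.4 contradicts itself and three other sections.

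The size is modest and rests on assumptions: about 7-14 of 136 patients at 5-10%, and about 1-2 revision events in total at a 15% revision rate. Power is a secondary issue. Without crossover dilution it stays above 80% at 10% withdrawal. With 5% crossover it drops to 78.9% at 5% withdrawal (65 per arm) or 78.6% at 10% (68 per arm), and only if withdrawn patients leave the analysis set. Selective loss is the main risk.

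**What to change.** In protocol 7.4, delete non-compliance as a ground for withdrawal. State instead that:

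- a missed visit, a missed CT or a switched method is recorded as a deviation;
- the patient stays in follow-up and is analysed under the allocated arm;
- when a visit is missed, revision, dysfunction, complications and death to 6 months are taken from available records, unless consent is withdrawn.

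In the same edit, reconcile:

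- 8.5 with 9.2.5, saying whether data from withdrawn patients are used;
- the as-treated wording in 7.4 with 8.4 and SAP 6.3.1;
- the SAP 4.4 full analysis set with protocol 11.4.1, which takes all randomised patients;
- the non-adherence rate, 1% in 7.4 and 5% in 11.2.

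The cost is a few sentences in each document and a little record review. Events treated at other hospitals may still be missed at a single centre, so the change reduces the selective loss without removing it.

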### **8.5 Data Collection and Follow-up for withdrawn participants**

Withdrawn patients will be clinically followed up as non-participants, 6-8 weeks postoperatively in our outpatient clinic. A second follow-up will be performed 6 months postoperatively including a native CT scan.

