### 9.2.2. Assessment of secondary outcomes

Operation time and anesthesia time in minutes: these times will be assessed at the operation day by anaesthesiology

Number of puncture attempts: this will be assessed at the operation day by the operating surgeon

Catheter placement (optimal vs. not optimal): between the 2nd and 5th postoperative day a CT scan will be made and VPS positioning will be assessed. Optimal catheter placement is defined as free-floating within the CSF without touching the ventricle wall or septum pellucidum, and the tip of the catheter located at the foramen of Monro showing an optimal length of the catheter. Catheters that did not fulfil all criteria have been defined as not optimal placed. Positioning of catheters will be further graded according to Yim et al. into grades I to IV (grade I: catheter terminates in the ipsilateral frontal horn, grade II: catheter terminates in contralateral frontal horn, grade III: catheter terminates in non-targeted CSF spaces, grade IV: catheter terminates intraparenchymally).

The cCT scan will be repeated during second follow-up after 6 months. This outcome will be assessed by partially blinded neuroradiologists.

Volumetry of side ventricles pre- and postoperatively in cm^3 (number and relative change): This will be assessed on the pre- and postoperative CT scans by partially blinded neuroradiologists.

Evan's Index pre- and postoperatively (number and relative change): This will be assessed on the pre- and postoperative CT scans by partially blinded neuroradiologists.

Complications (infection, bleeding, complications ass. with navigation method), mortality: rate and detail of complications will be assessed directly postoperative during the whole hospitalisation time and during the 1st and 2nd follow-up by the study nurse, the same accounts for mortality (including the reason for death if known).

Revision surgery (yes/no) and reason for revision: the rate of revision surgery as well as the indication for revision will be reported by the study nurse.

VPS dysfunction: the rate of VPS dysfunction will be assessed directly postoperative during the whole hospitalisation time, and during the 1st and 2nd follow-up by the study nurse.

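### Withdrawing patients after same-site revision for shunt dysfunction puts their later harm data, and possibly their place in the analysis, at risk

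*Combined protocol and SAP*

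**What the plan says.** **The withdrawal rule.** Protocol section 7.4 lists withdrawal of consent and non-compliance, and then "as well as patients with VPS dysfunction receiving revision surgery on the same side and location". It adds: "Patients will not be replaced".

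**The same events are outcomes.** Protocol section 4.3 names dysfunction and revision as safety aspects to be compared. Section 5.2 lists "Revision surgery (yes/no) and reason for revision" as a secondary outcome. Sections 5.4 and 11.4.5 list dysfunction and revision rate as safety endpoints. The schedule in section 9.1 has both assessed from the operation day to 6 months, and section 9.2.2 says that "the rate of revision surgery as well as the indication for revision will be reported by the study nurse".

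**After withdrawal.** Three instructions apply:
- Section 8.5: "Withdrawn patients will be clinically followed up as non-participants, 6-8 weeks postoperatively in our outpatient clinic", and then "A second follow-up will be performed 6 months postoperatively including a native CT scan".
- Section 9.2.5, on participants who stop prematurely: "No further assessments will be performed for such patients".
- Section 10.3: all adverse events are collected from consent to the last protocol procedure, with a safety follow-up period.

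**Analysis sets.** Protocol section 11.4.1 puts every randomised patient in the full analysis set (FAS). SAP section 4.4 restricts the FAS to randomised patients who completed follow-up, without drop-outs. SAP section 7 reports no changes from the protocol.

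**The concern.** Patients withdrawn under this clause have not refused anything. They leave because the shunt failed and was revised, which is one of the things the trial compares. Missing follow-up is then linked to outcome by design, and the number lost in each arm depends on how often that arm's shunts fail.

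The stated main objective is feasibility and safety. A safety comparison that follows patients without shunt failure to 6 months, but may stop following those with it, is incomplete where later harm is most plausible. Mortality is especially sensitive: protocol section 5.4 expects death or coma in under 1%, so one or two unrecorded deaths would change the picture.

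**Working it through.** **1. Does the clause act after randomisation?** Yes. Section 7.1 already excludes same-site revision surgery at entry. The clause stands under the withdrawal heading and concerns participants.

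**2. What is kept and what is exposed?**

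| Data | Protocol FAS (all randomised) | SAP FAS (no drop-outs) |
|---|---|---|
| Surgical intervention time, measured on the operation day | Kept | Could be lost |
| Triggering dysfunction and revision, with reason | Kept | Could be lost |
| Catheter position on the day 2-5 CT, if taken before the revision | Kept | Could be lost |
| Later infection, other complications, death, 6-month neurologic status and CT | Unclear: sections 8.5, 9.2.5 and 10.3 conflict | Could be lost |

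**3. Direction of bias for later harm.** Let r be the share of an arm withdrawn under the clause, p1 the chance that such a patient later has a first countable event (such as infection or death), and p0 that chance in the other patients. Take p1 and p0 as equal across arms. The true rate is (1 − r)p0 + r·p1.
- Withdrawn patients stay in the denominator and count as event-free afterwards: the observed rate is (1 − r)p0, a shortfall of r·p1.
- Withdrawn patients leave the denominator: the observed rate is p0, a shortfall of r(p1 − p0).

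The first shortfall always grows with r. The second does so if p1 exceeds p0, which is plausible after repeat surgery but is an assumption. In both cases the arm with more failures gains. A second revision adds nothing to a yes/no revision endpoint, so this applies to complications and death.

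**4. How many patients?** The documents give no revision rate. For an assumed share with same-site revision for dysfunction, applied to the protocol's 136 patients:
- 5%: 136 × 0.05 = 6.8, about 7
- 10%: 136 × 0.10 = 13.6, about 14
- 20%: 136 × 0.20 = 27.2, about 27

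**5. Primary outcome.** Inputs from protocol section 11.2: difference 15 min, SD 28.65 min, alpha 5%, power 80%. SAP section 4.2 makes the test two-sided.

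Plan's own figure: n = 2 × [28.65 × (1.960 + 0.842) / 15]² = 57.27, so 58 per group, as stated. The inflation 58 / (0.99 × 0.95²) = 64.9 gives 65 per group, also as stated. The protocol adds 6 patients to reach 68 per group and shows no calculation for them.

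Power = Φ(difference / (28.65 × √(2/n)) − 1.96), with n = 68 × 0.99 × (1 − r) per arm under the SAP FAS and the same r in both arms. The last column dilutes the difference for 5% crossover: 15 × 0.95 = 14.25 min.

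| Analysis set | n per arm | Power at 15 min | Power at 14.25 min |
|---|---|---|---|
| Protocol FAS | 67.3 | 85.9% | 82.3% |
| SAP FAS, r = 5% | 64.0 | 84.2% | 80.3% |
| SAP FAS, r = 10% | 60.6 | 82.2% | 78.2% |
| SAP FAS, r = 20% | 53.9 | 77.5% | 73.3% |

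The protocol FAS loses no power to this clause. The SAP wording loses some.

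**The case against.** **The revision endpoint is not lost.** A reader might infer that the trial stops counting revisions and dysfunctions. It does not: the triggering event is recorded with its reason, and the protocol FAS keeps the patient. Only the SAP's FAS wording could remove it. Even there the point is open, because SAP sections 6.3.1 and 6.4 promise an intention-to-treat analysis with missing data handled. This stands and limits the concern to what follows the first revision.

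**The clause is narrow.** It covers dysfunction with same-site revision. Revision at a new site, or for a reason that is not dysfunction, falls outside it. An all-revision rate would therefore overstate the number affected. This stands.

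**The 1% drop-out is not a fair yardstick.** One might set 7 to 27 withdrawals against the 1 or 2 patients implied by the planned 1%. That allowance is for deaths, in a calculation for an operation-day outcome. It was never a forecast of 6-month follow-up, so the contrast does not show a planning error.

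**Catheter position need not be biased the same way.** It is tempting to say that missing 6-month scans flatter the worse arm. A scan after revision may show a replaced catheter, so including it could equally hide a poor first placement. The direction is uncertain.

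**Clinical follow-up continues.** Section 8.5 schedules the visits and the CT, and section 10.3 requires adverse events to be collected. However, section 8.5 calls these patients non-participants and section 9.2.5 stops assessments, so neither provision ensures that the data reach the trial database.

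**The clause may be a misplaced entry criterion.** Its wording resembles the exclusion in section 7.1. Since that exclusion already exists and this text governs withdrawal, the plain reading is the one taken here.

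**Conclusion.** The point holds for data after the first same-site revision for dysfunction. As written, the plan makes an outcome event a ground for withdrawal and then gives conflicting instructions on whether later harms are study data. This can bias the 6-month complication and mortality comparisons, probably in favour of the arm with more shunt failures. That direction rests on later events being at least as likely after a revision as without one, and similarly so in both arms.

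The size is about 7 to 27 of 136 patients at an assumed 5% to 20%; no rate in the documents supports a narrower range. The primary outcome and the first-revision endpoint are safe under the protocol FAS. Under the SAP FAS these patients could leave both, and primary power at the full 15 min would fall from 85.9% to between 84.2% and 77.5% over that range.

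**What to change.** 1. Delete the revision clause from protocol section 7.4. Count revision as an outcome event and keep the patient in study follow-up to 6 months in the allocated arm. Leave withdrawal of consent and the separate pregnancy rule in section 10.3.2 untouched.
2. Reconcile protocol sections 7.4, 8.5, 9.2.5 and 10.3 so that the 6-8-week and 6-month visits and the CT already described in section 8.5 are entered as study data.
3. Align SAP section 4.4 with protocol section 11.4.1, so that these patients stay in the FAS with their primary outcome and their revision.
4. Use the day 2-5 CT for the comparison of randomised catheter placement. Flag 6-month imaging obtained after a revision, and report it separately or in a sensitivity analysis.

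**Cost.** Amendment wording, data entry, and the neurologic examination at the two follow-up visits, which section 9.3.5 describes as done only for the study and section 8.5 does not list for withdrawn patients. The current protocol is dated August 2024 with last participant out planned for February 2025, so most enrolment was probably complete. For patients already withdrawn, later events would have to be retrieved from clinical records where consent allows, and assessments never made cannot be recovered.
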